### Interventions

The standard of care for the treatment of locally advanced rectal cancer is TME. In patients with cT2N+, cT3N0, and cT3N+ mid-rectal tumors, the administration of nCRT, as well as the direct TME, are both considered guideline-concordant standard treatment approaches and are widely practiced [11,12]. In this study, data from patients undergoing TME as part of routine medical care will be collected prospectively. No additional interventions, treatments and follow-up protocols outside of standard care will be implemented. At the end of the study, patients will be categorized into two groups based on whether they received nCRT and the two groups will be compared in terms of primary and secondary endpoints. No treatment or monitoring protocols differing from routine practice will be proposed for patients or surgeons in the study. The natural prognosis of the treatment arms will be observed.

All the patients undergoing TME described as a precise dissection of the rectum along with the surrounding mesorectal tissue and all pararectal lymph nodes are eligible for the study [13].

**Direct TME Group:** Patients who undergo direct TME without neoadjuvant treatment.

**nCRT Group:** Patients who receive nCRT prior to TME.

Neoadjuvan CRT treatments include all conventional chemoradiotherapy regimens or total neoadjuvant chemoradiotherapy regimens (standard short or long course radiation and/or any standard chemotherapy regimen) described in European and American guidelines [11,12]. The details of radiotherapy and chemotherapy treatments will be recorded, including dosage, frequency, duration, complications, completion status, and the waiting period between treatments. Routine follow-up information for all patients including morbidity, radiologic assessments, recurrence, mortality be recorded in the database for the first five years post-surgery. Patient-reported quality of life scales will be recorded at baseline (prior to the initiation of treatment) and subsequently at 1, 3, and 5 years.

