#### Secondary outcome measures.

5-year DFS: The proportion of patients who remain free of disease recurrence (local or distant) five years after surgical intervention.3- and 5-year Overall Survival: The proportion of patients alive at 3- and 5-years post-treatment, regardless of disease status.3- and 5-year Local Recurrence Rate: The percentage of patients experiencing tumor recurrence at the primary site (anastomosis or pelvis) within 3 and 5 years.1-, 3- and 5- year Colorectal Cancer Specific Quality of Life: Patient-reported outcomes assessed using the New Cleveland Clinic Colorectal Cancer Quality of Life Questionnaire [14].1-, 3- and 5- year Bowel Dysfunction Related Quality of Life: Patient-reported outcomes assessed using the low-anterior resection syndrome (LARS) score [15].

Fig 1 represents the timeline of anticipated recruitment and outcome measures.

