### Statistical methods

During the study, missing data analyses and data quality assessments will be actively conducted, and measures to prevent data loss and enhance data quality will be implemented as appropriate. All statistical analyses will be conducted by experts from the TSCRS Biostatistics and Bioinformatics Analysis Unit using SPSS (SPSS Inc, Chicago, IL) software packages.

Multivariable regression analyses will be conducted to evaluate the effect of treatment strategy (direct TME vs. nCRT followed by TME) on the primary and secondary outcomes. The following covariates will be included in the models based on clinical relevance and literature review: age, sex, clinical T stage (cT2 vs. cT3), clinical N stage (N0 vs. N+), tumor differentiation, regimens of neoadjuvant treatment (long-course CRT, short-course RT, TNT with long or short-course RT), interval between neoadjuvant RT/CT and surgery, comorbidities (e.g., Charlson Comorbidity Index), performance status, postoperative complications (Clavien-Dindo), tumor histology, pathologic TME quality (pathologic completeness of the mesorectum), and center effect (as a random effect if appropriate).

For time-to-event outcomes such as disease-free survival (DFS) and overall survival (OS), Cox proportional hazards regression models will be used to estimate hazard ratios and 95% confidence intervals. The proportional hazards assumption will be tested using Schoenfeld residuals.

To address potential selection bias due to the non-randomized design, propensity score methods will be applied. Specifically, propensity scores for receipt of nCRT (vs. direct TME) will be estimated using logistic regression including the aforementioned covariates. The primary analysis will adjust for the propensity score as a covariate in the Cox model. Sensitivity analyses will be conducted using propensity score matching (1:1 nearest neighbor matching without replacement) and inverse probability of treatment weighting (IPTW) to ensure the robustness of results.

Patients lacking the main data specified in the inclusion and exclusion criteria, demographic data, or follow-up data related to the primary endpoint will be completely excluded from the study. Patients with missing data from other variables or secondary endpoints will only be excluded from those specific analyses, and secondary endpoints will be evaluated using data from patients with complete datasets.

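### The complete-dataset rule, with no baseline score among the listed covariates, leaves the quality-of-life and LARS comparisons liable to bias

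*Protocol article*

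**What the plan says.** Statistical methods in the protocol article fixes how missing secondary data are treated. One clause drops patients analysis by analysis: "Patients with missing data from other variables or secondary endpoints will only be excluded from those specific analyses". The clause after it sets who is analysed for these endpoints: "secondary endpoints will be evaluated using data from patients with complete datasets". The same section plans multivariable regression for the primary and secondary outcomes and introduces one list for all of them: "The following covariates will be included in the models based on clinical relevance and literature review". That list runs from age and sex to centre effect and contains no baseline questionnaire score. The propensity score is built from the same list.

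Interventions says: "Patient-reported quality of life scales will be recorded at baseline (prior to the initiation of treatment) and subsequently at 1, 3, and 5 years". Secondary outcome measures defines two questionnaire endpoints, each at 1, 3 and 5 years: "Patient-reported outcomes assessed using the New Cleveland Clinic Colorectal Cancer Quality of Life Questionnaire" and "Patient-reported outcomes assessed using the low-anterior resection syndrome (LARS) score". Neither is defined as a change from baseline.

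The article states no imputation, no repeated-measures model and no sensitivity analysis for missing data. Matching and inverse probability weighting are planned, but they address who received which treatment, not who answered the questionnaire.

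**The concern.** The Introduction gives the bowel, continence and sexual morbidity of nCRT as a main reason for asking whether it can be omitted. The questionnaire endpoints are where that gain would show.

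Two features of the plan work against a fair comparison:

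- **Complete cases only.** Patients who return questionnaires are probably fitter than those who do not. The article expects 80% 3-year DFS, so about 0.20 × 436 = 87 patients would have had an event by year 3, and they are plausibly less likely to complete an electronic survey. If loss depends on health differently in the two groups, the remaining patients are not comparable.
- **No baseline score in the models.** Treatment is chosen, not randomised, so balance in baseline function is not assured. The pre-treatment score is the direct measure of such imbalance, and it usually also explains part of the variation in later scores.

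**Working it through.** **Inputs from the article.** 436 patients, 218 per group (396 × 1.10 = 435.6, rounded to 436); assessments at baseline and at 1, 3 and 5 years. No sample size, response rate or effect size is given for the questionnaire endpoints, so there is no figure of the plan's own to reproduce for them.

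**Step 1: patients left under the rule.** Let r be the response per assessment (assumed). Per time point, 436 × r remain. If several assessments are required and responses are independent (assumed), 436 × r³ remain for the three follow-ups and 436 × r⁴ when baseline is also required.

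| r | Per time point | All three follow-ups | All four |
|---|---|---|---|
| 90% | 392 | 318 | 286 |
| 80% | 349 | 223 | 179 |
| 70% | 305 | 150 | 105 |

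Responses from one patient tend to be positively correlated, which moves the last two columns up towards the first. They are therefore pessimistic for a given r.

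**Step 2: effect of a baseline imbalance.** If the follow-up score has correlation ρ with baseline and the groups differ by δ SD at baseline, an analysis without the baseline score is off by ρ × δ. With δ = 0.2 and ρ = 0.3, 0.5 or 0.7 (assumed), that is 0.06, 0.10 or 0.14 SD.

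**Step 3: simulation.** All inputs are assumed: 400 replicates, 218 per group, true difference 0.40 SD, ρ from 0.3 to 0.7, about 65–70% of patients responding, one follow-up time and no other covariates. Each cell gives the mean complete-case estimate over the range of ρ.

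| Scenario | Without baseline score | With baseline score |
|---|---|---|
| Balanced, missing completely at random | 0.39–0.41 | 0.40–0.41 |
| 0.2 SD imbalance, missing completely at random | 0.47–0.54 | 0.40–0.41 |
| Balanced, loss depends on baseline score in one group only | 0.27–0.33 | 0.40–0.41 |
| 0.2 SD imbalance and that same loss | 0.38–0.40 | 0.39–0.41 |
| Balanced, loss depends on follow-up score equally in both groups | 0.36–0.37 | 0.37–0.38 |
| Balanced, loss depends on follow-up score in one group only | 0.16 | 0.18–0.28 |

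The second row agrees with step 2 (0.46, 0.50, 0.54). The table shows three things:

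- Without the baseline score, the error can go up, go down or cancel.
- Including the score repairs imbalance and loss driven by baseline.
- Including it does not repair loss driven by the unobserved follow-up score.

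**Step 4: precision.** Adjusting for baseline reduces residual variance by ρ²: 9%, 25% or 49% at ρ = 0.3, 0.5 or 0.7.

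**The case against.** **Bias is not shown.** A reader might infer that the comparison will be biased. The article gives no response rates, no loss by group and no baseline scores, and the first row of the simulation shows no bias in the benign case. The plan also assumes equal DFS in the two groups, so loss caused by recurrence alone could be similar in both. This stands: the claim is that the analysis is liable to bias, not that it is biased.

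**Disregard of the baseline score is an inference.** A reader might take the list as a decision not to use it. The article does not say so, and an analysis plan that is not shown could add it. Interventions also does not name LARS when it describes the baseline scales, so a baseline LARS score is uncertain. What remains is that the article names the covariates for the secondary-outcome models and the propensity score, and this one is not among them.

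**The large losses need the harsher reading.** Exclusion only from the specific analyses affected, with endpoints defined separately by year, points towards a per-time-point rule. The reference to complete datasets points the other way. Neither reading can be ruled out, so 179 or 286 should not be quoted without 349 or 392.

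**Scope and weight.** The rule is worded for all secondary endpoints, so a reader might extend the point to 5-year DFS and overall survival. Those go into Cox models, which can censor, and the argument does not carry over. The primary analysis and sample size are untouched.

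**Prevention is planned.** The article promises data-quality work and weekly completeness checks. These may reduce the amount missing; they do not change the analysis rule.

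**Conclusion.** The point holds for the two questionnaire endpoints. The complete-data rule is stated, not merely left open, and the named covariates omit a score that the article says is collected before treatment. In a non-randomised cohort this leaves the comparison open to bias when response or baseline function differs by group, and it wastes precision in any case.

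The size cannot be fixed from the document. Under the assumed inputs, a true difference of 0.40 SD was estimated anywhere from 0.16 to 0.54 without the baseline score, and correctly when data were missing completely at random and baselines were balanced. The number of patients retained depends on the assumed response rate and on which reading of the rule is meant. The change should be made, but it concerns secondary endpoints only.

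**What to change.** For the Cleveland Clinic questionnaire and LARS endpoints, replace the complete-dataset rule as follows:

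- Analyse each score with a mixed model for repeated measures using all available assessments, with baseline score, treatment, time, treatment-by-time and pre-treatment covariates.
- Add the baseline score to the propensity model used for these endpoints. State whether LARS itself is recorded at baseline and, if not, which baseline score is used. State how a missing baseline score is handled.
- Say that scores are compared among patients alive at each time, and report the numbers alive and responding by group. Scores after death do not exist and should not be implicitly filled in.
- Keep complete-case analysis as a sensitivity analysis, and state whether it is per time point or requires every assessment.
- Add a missing-not-at-random sensitivity analysis, for example shifting unobserved scores by a range of amounts separately by group. The last simulation row shows why baseline adjustment alone is not enough.

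The cost is a change of wording and some extra analysis; no data collection is added where the baseline score is already planned. The downside is reliance on a missing-at-random assumption, which the last item is there to test. The mixed model itself was not simulated here.

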### The data monitoring committee and interim analyses

Two members of the steering committee (TB, AEC) are responsible for data monitoring. These investigators will coordinate with the data processing secretary employed by the sponsor (TSCRS) to check the reliability and completeness of the data on a weekly basis. They will present reports to the steering committee every month and to the participant investigators twice a year. They are responsible for interim analysis and adverse event monitoring every six months.

The interim results of the study will be shared at national and international meetings and conferences as the primary and secondary endpoints are reached (in 1, 3 and 5 years after intervention). After completion of the study, the results will be prepared as a manuscript and published in a journal as well as clinicaltirals.gov.

The data monitoring committee members are affiliated with the sponsor, TSCRS, which is a non-profit professional association, and all investigators who are going to be invited in this study are members of this association. An independent monitoring committee has not been established for the study.

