## Methods

### Study setting

The CANO protocol has been designed by six principal investigators (steering committee) affiliated with five tertiary referral hospitals in Türkiye (Baskent University Hospital, Istanbul Health and Technology University, Dokuz Eylul University Hospital, Halic University Memorial Sisli Hospital and Acibadem Kent Hospital) which are specialized in the treatment of colorectal cancer. The study is coordinated by the study chair (FK) from Baskent University. The steering committee includes two members responsible for writing and updating the protocol (CA, TB), two members responsible for study secretariat and communication with participant centers (IEB, OB), and two members responsible for data storage, reliability, monitoring and safety (TB, AEC).

All centers in Türkiye implementing a multidisciplinary approach to rectal cancer will be invited to participate in the study by Turkish Society of Colon and Rectal Surgery (TSCRS). The clinical administrative officer or department head of all centers will be reached by e-mail. The details of the protocol have been announced on the webpage prepared by the steering committee (https://arastirma.tkrcd.org.tr/). Centers invited to participate in the study will be informed through this website and will also receive additional information via a webinar organized by TSCRS.

In accordance with the guidelines of the Turkish Ministry of Health – Drug and Medical Devices Agency, centers that agree to participate in the study must submit a letter of support to TSCRS on behalf of the study chair (FK). This support letter must include the permission of the institutional data sharing; the signatures of the supervising researcher and clinical administrative officer/department head. Centers that submit their letters by the specified deadline (1 August 2025 anticipated) will be added to the study sites list as an update in the protocol on clinicaltrials.gov.

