### Trial registration and ethical considerations

The study protocol has been prepared in accordance with SPIRIT guidelines (S1 File) and approved by Baskent University Ethical Review Board on 15-06-2025 (Approval number: KA24/461). The trial protocol has been registered before starting inclusion (NCT06823297, ClinicalTrials.gov). The study has not started patient recruitment yet and the anticipated recruitment date is 01.08.2025. The anticipated timeline is as follows: Primary recruitment completion: August, 2030, study completion: August, 2030.

Written informed consent for inclusion in the study will be obtained from all eligible patients prior to any treatment (neoadjuvant treatments or surgery), in conjunction with the treatment consents. A distinct informed consent form for the study, prepared by the steering committee and approved by the ethics committee, exists separately from the institutional informed consent form. The attending surgeon is responsible for providing the patient with comprehensive information regarding the study and securing this consent in written form. Another healthcare provider (nurse, resident, surgeon) will witness the consenting process.

In this study, participant data and biological specimens are not being collected for ancillary studies. However, each institution participating in the study may include statements in their own surgical informed consent forms regarding the use of patient information and specimens in other studies. This responsibility lies with the respective institution and the surgeon.

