### Sample size and recruitment

The literature reports a mean 3-year disease-free survival rate of 75–85% for the sample to be included in the study [16]. For patients with mid-rectal tumors (cT2N+ and cT3N0) without high risk MRI findings, the 3-year disease-free survival rate was estimated to be 80% for both direct TME and TME following neoadjuvant chemoradiotherapy. Under these conditions, with α = 0.05 (95% confidence interval) and 80% power, the power analysis indicated that a total of 396 patients (1:1 ratio) would be required. Considering a 10% dropout rate, it is planned to include 218 patients in each group, for a total of 436 patients.

According to data from the Turkish Ministry of Health, General Directorate of Public Health, a total of 24,312 patients were diagnosed with rectal cancer between 2020 and 2024, of whom 17,896 underwent surgery (https://hsgm.saglik.gov.tr/tr/kanser.html). Since this study will be conducted nationally under the sponsorship of the main society of Turkish colorectal surgeons TSCRS, we anticipate reaching the targeted patient number within five years from the start of the study. To achieve this goal, TSCRS will utilize various channels, including mailing, social media, and its website, to announce the study and inform surgeons about the protocol.

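### Interim results may be presented at meetings while recruitment is open, so in this non-randomised cohort released comparative results can influence which treatment later patients receive

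*Protocol article*

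**What the plan says.** The section on the data monitoring committee and interim analyses states: "The interim results of the study will be shared at national and international meetings and conferences as the primary and secondary endpoints are reached". The times given are "in 1, 3 and 5 years after intervention". The full report comes later: "After completion of the study, the results will be prepared as a manuscript and published in a journal". The same section says that the two monitoring members run interim analyses every six months and that participating investigators receive reports twice a year, without saying what those reports contain. It adds that every invited investigator is a member of the sponsoring society.

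On timing, the section on trial registration and ethical considerations says "the anticipated recruitment date is 01.08.2025" and gives "Primary recruitment completion: August, 2030, study completion: August, 2030". The sample size section agrees: "we anticipate reaching the targeted patient number within five years from the start of the study". The section on adverse events and discontinuation says the study goes on until the required number is reached.

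On group membership, the Interventions section says: "At the end of the study, patients will be categorized into two groups based on whether they received nCRT". Treatment follows routine care, and the exclusion criteria remove patients treated without a multidisciplinary council decision.

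The Statistical methods section lists the covariates for the regression models and uses the same list for the propensity score. Neither calendar time nor enrolment period is on it. The section on access to data restricts who may open the patient database. It sets no rule on releasing results.

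**The concern.** In a randomised trial, early knowledge of results does harm, but it cannot change which arm the next patient is assigned to. Here it can. Clinicians and their councils decide on nCRT for each new patient, and they are among the people who would hear the results.

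The order of release adds to the concern. The only endpoints at 1 year are quality of life and LARS. The Introduction attributes bowel dysfunction and incontinence to nCRT, so the article itself gives reason to expect the first results to favour omitting it. Disease-free survival, overall survival and local recurrence start at 3 years. Functional results could thus move practice before the oncological question is answered.

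Two things are at stake. If practice shifts, early and late recruits may differ in how they were selected for treatment, and the analysis as listed has no term for enrolment period. A shift would also make the planned 218 per group harder to fill evenly.

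**Working it through.** **The plan's own total.** The article gives 396 patients, then 436 after a 10% allowance. With 80% disease-free survival in both groups, and assuming a 10-point non-inferiority margin and one-sided alpha 0.05 (the sample size section states neither), n per group = (1.645 + 0.842)² × 2 × 0.80 × 0.20 / 0.10² = 198, or 396 in total. Then 396 × 1.10 = 435.6, taken as 218 × 2 = 436. The calculation below uses only 436 and the five-year recruitment period.

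**Overlap of release with recruitment.** Assumptions: uniform accrual over 60 months, outcomes dated from about entry.

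- Enrolled after the first patient reaches 1 year: (60 − 12)/60 = 80%; 0.80 × 436 = 349.
- Enrolled after the first patient reaches 3 years: (60 − 36)/60 = 40%; 0.40 × 436 = 174.
- Enrolled after the first patient reaches 5 years: (60 − 60)/60 = 0%, unless recruitment overruns.

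These are maxima. They start the clock when a single patient has the outcome, and nobody presents one patient. The outcomes also run from surgery or intervention, while consent comes before any treatment, so patients given nCRT reach each time point later after entry.

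**A more realistic release point.** Assume, for illustration, release once 50 patients have the outcome. Accrual is 436/60 = 7.3 per month, so 50 patients are enrolled by about month 7. Release falls at about month 7 + 12 = 19 and month 7 + 36 = 43. Still to enrol: (60 − 19)/60 = 68% and (60 − 43)/60 = 28%, before any reporting lag.

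**What early 3-year results would be worth.** Assume equal groups and true 3-year disease-free survival of 80% in both. The standard error of the difference is √(2 × 0.80 × 0.20 / n), with n per group.

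| Years from start | Patients with 3-year outcome | Still to enrol | 95% CI half-width | Chance of a difference beyond 10 points |
|---|---|---|---|---|
| 3.5 | about 44 | about 131 (30%) | about 24 points | about 0.41 |
| 4 | about 87 | about 87 (20%) | about 17 points | about 0.24 |
| 4.5 | about 131 | about 44 (10%) | about 14 points | about 0.15 |

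At year 4, for example, n is about 43.6 per group, the standard error is √(0.32/43.6) = 0.086, and 1.96 × 0.086 = 0.168. Two truly equal treatments would appear more than 10 points apart about one time in four, while a fifth of the cohort was still to be enrolled.

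**The case against.** Several objections limit the point.

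- **Comparative release is not stated.** The sentence speaks of interim results, not results by group, and the Interventions section places the grouping and comparison at the end of the study. A reader might infer that by-group presentations are definitely planned; the article does not say so. However, the stopping rule compares arms, so by-arm figures must exist during the study, and nothing keeps them out of presentations or the twice-yearly investigator reports.
- **Endpoints may be reached by the whole cohort.** That would remove the overlap. It fits poorly with the word interim and with study completion in August 2030: a patient enrolled that month reaches 1 year in August 2031 and 3 years in August 2033. If it is the intended meaning, the proposed sentence only makes it explicit.
- **Influence is possible, not certain.** A reader might infer that the results will steer treatment. The documents support only that they can. Surgeons do not decide alone, since a council decision is required.
- **A change in uptake is not by itself bias.** An adjusted comparison is biased only if enrolment period is also related to prognosis, or if selection shifts on unmeasured factors. Neither is shown here. The Limitations section already concedes residual confounding and possible changes in practice, but conceding them does not remove a source that the study itself controls.
- **The adjustment could be left to an analysis plan.** Often it could. Here, though, the article gives an explicit covariate list and ties the propensity model to it.
- **Role overlap.** One of the two monitoring members is also one of the "two members responsible for writing and updating the protocol". A reader might infer that moving this role would protect the study. It would do little: the whole steering committee has database access and receives monthly reports.

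**Conclusion.** The point stands in a limited form. On the stated timeline, 1-year and first 3-year results can be made public while recruitment is open, in a cohort where the clinicians' choice defines the groups, and no rule holds comparative results back. This is an avoidable route to selection that changes over time, and the listed adjustment does not cover it.

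The exposure is at most about 80% of patients for 1-year results and at most about 40% for 3-year results. Under the 50-patient illustration it is about 68% and 28%. All four figures rest on uniform accrual over 60 months. The size and direction of any resulting bias cannot be derived from the document.

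Two stronger readings should be resisted. The 5-year results do not overlap with recruitment as planned; they do so only if it runs past August 2030. Nor does the argument support withholding results until the 3-year primary analysis, because the route by which they could affect treatment choice within the cohort closes when recruitment closes.

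**What to change.** In the section on the data monitoring committee and interim analyses, replace the sentence on sharing interim results with wording such as: no results by treatment group will be presented publicly or given to participating investigators until recruitment has closed; until then, reports to investigators and to meetings are limited to accrual, data completeness and outcomes pooled over both groups; safety looks by group stay with the members responsible for monitoring.

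In the Statistical methods section, add enrolment period to the covariates of the propensity model.

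The first change is one of wording and the second adds one covariate. Neither changes the sample size, adds staff or interferes with the six-monthly safety review. The cost is that no comparative results can be presented at conferences during recruitment. Enrolment period is a safeguard against measured shifts over time; it does not replace holding the results back.
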